#### 6.1.2 Secondary study parameters/endpoints (if applicable)

Secondary study parameters/outcomes include (see page 26 for follow-up schedule):

- Achalasia symptoms (Eckardt score); Health-related- and disease specific QoL (Pediatric Quality of Life inventory (PedsQL) 4.0, Gastro-intestinal QoL (Pediatric Quality of Life inventory – GI) and Achalasia disease specific QoL questionnaire (DSQoL)) (37-39, 55)

- Reflux symptoms (reflux disease questionnaire, RDQ)
- LA grade (EGD)
- 24 hour pH-impedance (pH-MII) measurement parameters (Table 1)
- HRM parameters (Table 1)
- Procedure times
- Complications (any unwanted events that arise following treatment and/or that are secondary to the treatment)
  - o Severe: resulting in admission >24 hours or prolongation of an already planned admission of >24 hours, admission to a medium or intensive care unit, additional endoscopic procedures, blood transfusion or death.
  - o Mild: all other complications.

## **6.2 Randomization, blinding and treatment allocation**

When participants are recruited for the study, the time to consider participation is up to four weeks. Before randomization, the patient (if  $\geq 12$  years) and all legal guardians (if patients <16 years) must have signed the informed consent form.

Randomization will be performed by using a web-based program (Castor electronic data capture (EDC) system) and will be stratified per center, to reach equal number of patients treated with POEM or EBD in each center. To ensure balance of treatment groups, stratified block randomization with randomly selected block sizes in order to minimize selection bias will additionally be performed within each center. Castor EDC will generate the allocation sequence. Allocation concealment is applied to all investigators, clinicians and patients. One blinded central reader will analyze all HRM and pH-MII measurements and a second blinded central reader will analyze all barium esophagrams.

## **6.3 Study procedures (see figure 2 below for study flow chart, page 26)**

### **Inclusion criteria**

The combination of Eckardt symptom score, a timed barium esophagram and HRM gives a complete picture of the esophageal function and are considered standard investigations to diagnose achalasia.

## Baseline

At baseline, the following measurements and questionnaires will be performed:

- Standard achalasia care:
  - Body weight and height and body mass index (BMI) including respective z-scores
  - Medical history
  - PedsQL 4.0 (41, 42)
- Additional study measurements and questionnaires
  - Disease specific QoL (43)
  - Reflux disease questionnaire (44)
  - PedsQL-GI 3.0 (55)

Questionnaires regarding reflux, achalasia specific quality of life and gastro-intestinal quality of life (see Appendix A) are not currently implemented in standard achalasia care. These two questionnaires take maximum 15 minutes to fill in and are not considered burdensome for patient's psychological well-being.

## Follow-up

At 12 months follow-up, the following study procedures are performed in all study participants:

- Barium esophagram
- HRM
- pH-MII
- EGD

In clinical practice, these tests are performed when symptoms or complications suggestive of achalasia recurrence and/or GER. Recent recommendations involve an EGD and pH-MII 1 year post-therapy in order to evaluate the presence of GERD in all achalasia patients. In this study, we also perform a barium esophagram and HRM post-therapy in order to obtain a complete overview of the esophageal function.

Figure 2: Flow chart of study visits and measurements.

[figure not shown]

|               |  |  |   |
|---------------|--|--|---|
| pH-MII*       |  |  | X |
| EGD+biopsies* |  |  | X |

**Figure 2:** flow chart of study visits and measurements. Measurements shown in grey indicate standard achalasia care whereas measurements in green indicate that they are not considered standard care.

\*BMI = body mass index; RDQ = reflux disease questionnaire; PedsQoL = Pediatric quality of life inventory; PedsQoL-GI = Pediatric quality of life inventory – Gastro-Intestinal Symptoms; HRM = high resolution manometry; EGD = esophagogastroduodenoscopy

### ***Esophageal Balloon Dilation (EBD)***

In this study EBD will be performed by experienced (pediatric) gastroenterologists that have independently performed at least 15 procedures. The procedure will be recorded on video to make evaluation afterwards possible. Pictures to evaluate LA grade of GERD will be taken.

Patients will be treated under general anesthesia with endotracheal intubation.

Patients are asked to use a diet with fluids starting at least 48 hours before the procedure, only clear fluids starting 24 hours and nil per mouth starting 8 hours before the procedure.

Initial EBD treatment will consist of a series of two dilatation sessions, scheduled two weeks (10-18 days) apart. In the first session, two dilations of one minute each with a dilatation pressure of respectively 5 and 8 psi will be performed using a single-use low-compliance 30 mm balloon under radiological guidance. The second treatment session is identical but with a larger balloon with a diameter size of 35mm. Patients are discharged without any diet restriction.

If patients in the EBD treatment arm have persisting symptoms, a subsequent dilation with a 35-mm balloon is performed. If a patient has a relapse (recurrent symptoms and evidence of active disease on barium esophagram and/or HRM) a second series of two EBD sessions is performed. This is considered **part of the initial EBD** treatment. If symptom recurrence occurs after a third EBD or second series of two EBDs, this is considered as 'treatment failure'.

Relapse therapy will then be offered at the discretion of local preferences of the attending physician.

***Peroral endoscopic myotomy (POEM)***

POEM will be performed by experienced (pediatric) endoscopists, who have independently performed over 15 procedures. Patients are admitted two hours prior to the POEM procedure and are scheduled to be discharged within 48 hours post-procedure. Patients are asked to use a diet with clear fluids starting 48 hours before the procedure and nil per mouth starting 8 hours before the procedure. On the day of the procedure, antibiotics and double dose PPI are administered intravenously (see page 28 and 29 for medicament and dosage). The mouth, throat and esophagus are rinsed with saline and chlorhexidine (40–60 ml). POEM procedures are then performed as described by Inoue et al. The endoscopic procedure will be recorded on video to make evaluation afterwards possible. Pictures to evaluate LA grade of GERD will be taken. A forward-viewing upper endoscope is used with a transparent distal cap. Carbon dioxide gas is used for insufflation during the procedures. An endoscopic dissection knife is used to access the submucosa, to create the submucosal tunnel, and also to divide circular muscle fibers over a minimum length of 6 cm in the esophagus, and 2 cm onto the cardia according to the standards of surgical myotomy. An electrogenerator is used with Endocut Q mode (effect 2) to open the mucosa, and spray coagulation mode (effect 2, 50 watt) to dissect the submucosa and divide the muscle fibers. A coagulating forceps is used for hemostasis as needed. Closure of the mucosal entry site is performed using standard endoscopic clips.

Patients are discharged with a soft diet for 2 weeks.

*Reflux surveillance*

GERD may develop post-achalasia intervention due to disruption of the LES. A recently performed randomized controlled trial in adult achalasia patients showed a higher incidence of GERD in patients who were treated with POEM (31% grade A; 4% grade B, 8% grade C) compared to those treated with EBD (7% grade A),  $p=0.002$ . In a recently published literature review, GERD was present in 8% of children treated with EBD vs 28% of children treated with POEM.(26) However, in these included pediatric studies, GERD was defined with varying criteria and diagnostic tests and many studies were retrospective in design. A true estimate of the occurrence of GERD post-achalasia treatment, will only be possible by prospective evaluation using standardized tools (i.e. EGD with biopsies and pH-MII). As a precautionary measure, all study patients will take PPIs orally in a single daily dose starting at the day after treatment (esomeprazole,  $<20\text{kg} = 10\text{mg/day}$ , ;  $\geq 20$

kg= 20mg/day for at least one year (+/- 6 weeks) after initial therapy. At 12 months after randomization (+/- 6 weeks), an EGD, HRM and pH-MII will be performed after cessation of PPI 4-6 weeks prior to investigations (Figure 4). In case of abnormal pH-MII and/or EGD results, the attending physician will follow-up and manage GERD according to latest recommendation guidelines pediatric GERD, which may include adjustment of PPI dose and repeat pH-MII/EGD.(46) In case of normal pH-MII and EGD results, PPIs can be ceased.

[figure not shown]

**Figure 4: study flow chart**

## General follow up

Individual procedures during follow up of the study are outlined at page 26 in figure 2.

Apart from these structured follow-up moments, additional tests (e.g. timed barium esophagram, and HRM) can be performed at any time if a subject reports relapse symptoms as per standard achalasia care.

Follow-up visits, measurements and questionnaires should best be performed according to the schedule below. Variations from the schedule will be accepted within limits as follows (table 2):

**Table 2: accepted variations from the study schedule:**

| Study moment | Accepted variations |
|--------------|---------------------|
|--------------|---------------------|

|                                                      |                                                               |
|------------------------------------------------------|---------------------------------------------------------------|
| Second EBD session (part of primary therapy)         | 1 – 6 weeks after first EBD session                           |
| T=3 months follow-up                                 | -2 weeks, + 4 weeks                                           |
| T=6 months follow-up                                 | +/- 6 weeks                                                   |
| Monthly measurement of weight in the first 12 months | +/- 2 weeks. A maximum of 25% missed measurements is allowed. |
| HRM, pH-MII and EGD at T=12 months                   | +/- 6 weeks                                                   |
| Cessation of PPI prior to measurements               | - at least 14 days before pH-MII
- 4 – 6 weeks before EGD  |

### *Questionnaires*

The Eckardt score is developed to objectify achalasia symptoms and is the sum of symptom scores for dysphagia, regurgitation, chest pain and weight loss.(47) It is commonly used in both adults as well as children. Each symptom is scored from 0 to 3. The minimum score is 0, the maximum 12. (see Appendix A).

The reflux disease questionnaire is developed to objectify frequency and severity of GER symptoms and is commonly used in pediatric and adult patients.(44)

It consists of 12 items that cover the symptoms heartburn, regurgitation and upper abdominal pain. Each item can be rated from 1-6. A mean score is calculated from all 12 respective answers.

The Pediatric quality of life inventory (PedsQL V4.0) assesses children's and parent's perception of child health related quality of life.(42) The PedsQL consists of four domains (physical, emotional, social and school) and has 23 items. Each item can be rated from 0 – 4. After completion of the questionnaire, the cumulative total score is calculated.

The Gastro-intestinal Pediatric Quality of Life inventory (PedsQL-GI 3.0) assess children's and parents perception of child gastro-intestinal health related quality of life. (55) The PedsQL-GI consist of 74 questions on gastro-intestinal symptoms. Each item can be rated between 0-4, the cumulative total score is calculated.

The achalasia disease specific QoL questionnaire consists of 20 items in three domains (swallow difficulties, family and friends and emotions) that measure disease specific QoL.(43)

### **Measurements**

#### *Timed barium esophagram*

In the timed barium esophagram technique, upright frontal spot films of the esophagus are obtained at 1 min after ingestion of low-density (45% weight in volume) barium sulphate. This is a routine clinical test that is used to measure esophageal emptying and esophageal function when (recurrence of ) achalasia is suspected.

Barium esophagram protocol:

- Ruler is placed on patient's back in order to measure column height
- Patient swallows barium contrast in upright position
  - 7 – 10 years: 100 cc
  - 10-14 years: 150 cc
  - 14-18 years: 200 cc
- Radiologic films are taken immediately after ingestion of barium (t=0), 1 minutes after barium ingestion
- A barium esophagram is considered abnormal when esophageal stasis occurs  $\geq 1$  minute after ingestion.

#### *High resolution manometry (HRM) of the esophagus*

HRM of the esophagus (pressure measurement) is the gold standard to diagnose achalasia and is used in clinical practice to evaluate the effect of the treatment. The latest CC is used for the evaluation of esophageal motility disorders and is able to detect three different subtypes of achalasia (type 1 = classic; type 2 = panesophageal pressurization; type 3 = spastic).(39)

Intraluminal impedance can be measured in conjunction with pressure (i.e., high-resolution impedance manometry, HRIM). Pressure and impedance channels are then incorporated into one catheter. In some participating centers, only a HRIM catheter is available. As the followed

procedure and patient discomfort (catheter size, duration) for these tests are identical, both HRIM and HRM catheters can be used in this study.

#### *pH-impedance (pH-MII) recording*

Adult patients are prone to develop GERD post-EBD or post-myotomy (both laparoscopic and endoscopic) and often have a high esophageal acid exposure time.(7, 27, 48) To objectively evaluate GERD, pH-MII recording is therefore indicated. A pH-MII measurement is a routine clinical test for the assessment of esophageal acid exposure in adults and children. It is currently considered the best available test to correlate symptoms with all types of reflux episodes (i.e. acid and weakly acidic reflux).(49) Multiple studies in adult patients have demonstrated that after myotomy (either LHM or POEM), typical symptoms, such as heartburn and bitter-tasting regurgitation, are poor correlates of objective distal esophageal acid exposure as measured by 24-h pH-MII.(50, 51)

During the 24h pH-MII test, a small catheter is introduced transnasally into the esophagus.(52) If possible, the catheter is placed during EGD under anesthesia. This catheter consists of impedance and pH sensors that measure reflux episodes and esophageal acid exposure. Data are stored on a datalogger that is carried by the patient in a small backpack or shoulderbag. PPI's will be ceased at least 14 days prior to the pH-MII study. See table 1 for pH-MII parameters that are analyzed.

#### *Esophagogastroduodenoscopy (EGD)*

EGD is performed under general anesthetics, as per routine clinical care in pediatrics. Biopsies are routinely taken to evaluate the presence of esophagitis.(53) See table 1 for EGD parameters that are analyzed.

After treatment, the main clinical reason to perform EGD is to investigate whether reflux related esophagitis is present. The degree of esophagitis is scored according to the LA classification.(53) PPI therapy is stopped 4-6 weeks before the endoscopy as is standard in clinical practice when the continuing need for PPI therapy is evaluated.

#### **6.4 Withdrawal of individual subjects**

Parents and/or patients can redraw subjects from the study at any time for any reason if they wish to do so without any consequences. The investigator can decide to withdraw a subject from the study for urgent medical reasons.

If a subject refuses one of the study measurements during follow-up, but is otherwise willing to continue study participation, he/she will remain in follow-up for assessment of primary outcome at  $t=12$  months. In case a patient does not adhere to the protocol, or is lost to follow-up, available data from the last included timepoint are used for estimation of the primary endpoint in an intention to treat analysis.

#### **6.5 Follow-up of subjects withdrawn from treatment**

If a subject gets withdrawn from the study, he/she will have the standard achalasia care, depicted in figure 1. In case of treatment failure after study withdrawal, therapeutic approach will be decided based on shared decision making and the discretion of the attending physician.

If a subject refuses one of the study measurements during follow-up, but is otherwise willing to continue study participation, he/she will remain in follow-up.

#### **6.6 Premature termination of the study**

Efficacy and safety data of the study will be monitored independently by the investigators, mainly by the PI, and the DSMB. Safety of the study subjects is the most important issue. After the first 50 patients have reached follow-up moment  $T=12$  months, the DSMB will discuss the data and safety and review the stopping regulations. The study can be terminated early in case of safety issues.

## **7 SAFETY REPORTING**

### **7.1 Temporary halt for reasons of subject safety**

In accordance to section 10, subsection 4, of the WMO, the sponsor will suspend the study if there is sufficient ground that continuation of the study will jeopardize subject health or safety. The sponsor will notify the accredited MREC without undue delay of a temporary halt including the reason for such an action. The study will be suspended pending a further positive decision by the accredited MREC. The investigator will take care that all subjects are kept informed.

### **7.2 AEs and SAEs**

#### **7.2.1 Adverse events (AEs)**

Adverse events are defined as any undesirable experience occurring to a subject during the study, whether or not considered related to the intervention. All adverse events reported spontaneously by the subject or observed by the investigator or his staff will be recorded.

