**Additional investigations**

- EGD at T=12 months
- Contrast esophagram at T=12 months
- pH-MII at T=12 months
- HRM at T=12 months
- RDQ and QoL questionnaires at T=3, 6, and 12 months)
- Weight assessment at home on a monthly basis until T=12 months
- Eckardt score on a monthly basis until T = 12 months

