## 5 TREATMENT OF SUBJECTS

### 5.1 Investigational product/treatment

In this study, the investigational treatment is POEM. This procedure is performed as described by Inoue et al.(5) For a detailed description of the procedure see under Methods, Section 4.

'Initial therapy' is defined as:

- POEM: a single POEM procedure
- EBD: a series of two EBD sessions, scheduled two weeks apart (see page 29 for allowed variations from the study schedule).
  - In case of *persisting* symptoms as evaluated 7 days after the second EBD session, a third EBD session (35mm in children <12 years; 40mm in children ≥12 years old) will be performed 2-4 weeks after the second. Persisting symptoms in this regards are defined as an Eckardt score >2. Note that a lower score is considered positive (as compared to diagnosis / relapse) due to the fact that the evaluation of weight loss within a week after treatment is considered inaccurate.
  - In case of *relapse* (defined as recurrent symptoms (Eckardt score >3) and evidence of active disease on barium esophagram and/or HRM), a second series of two EBD 2-4 weeks apart will be performed as part of the initial therapy. For this second series a 30 & 35mm balloon is used in children <12 years and a 35 & 40mm balloon is used in children ≥12 years old).

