### **7.3 Safety reporting**

#### **7.3.1 Adverse events**

Adverse events occurring from the first study-related procedure until 30 days after protocol treatment will be recorded in the CRF.

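### Adverse events are captured passively while staff contact and the recording window differ by arm, so the comparison of minor harms is unreliable, with uncertain direction of bias

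*Protocol*

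**What the plan says.** **Capture.** Section 7.2.1: "All adverse events reported spontaneously by the subject or observed by the investigator or his staff will be recorded". Section 7.3.1: "Adverse events occurring from the first study-related procedure until 30 days after protocol treatment will be recorded in the CRF". Neither section describes a question put to every family about harms.

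**Contacts in the EBD arm.** Section 6.3 (EBD): "Initial EBD treatment will consist of a series of two dilatation sessions, scheduled two weeks (10-18 days) apart". Table 2 accepts a second session "1 – 6 weeks after first EBD session". Section 5.1 adds a symptom check "as evaluated 7 days after the second EBD session". If symptoms persist, a third session follows two to four weeks after the second. If the child relapses, a second series of two sessions also counts as initial therapy.

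**Contacts in the POEM arm.** Section 5.1 defines the treatment as one procedure. Section 6.3 (POEM) says that patients "are scheduled to be discharged within 48 hours post-procedure". The next visit named in the text is at three months (section 2, secondary objectives). Section 9.4, on COVID-19, likewise lists the outpatient visits as months 3, 6 and 12.

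**Contacts common to both arms.** Figure 1 lists a monthly home weight and "Eckardt score on a monthly basis until T = 12 months". Section 6.3 (Questionnaires) limits the Eckardt score to dysphagia, regurgitation, chest pain and weight loss.

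**Use of the data.** Safety is part of the primary objective (section 2). Procedure-related complications, graded mild or severe, are a secondary outcome (sections 2 and 6.1.2). All adverse events go into the DSMB's interim report (section 7.4).

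**The concern.** When capture is passive, the number of recorded events depends on the chance to report or observe them as well as on the true rate. Here that chance is set by the treatment schedule. Two arms with the same true rate of fever or pain at home could show different recorded rates. Blinding is stated for the end-point committee and the central readers, not for the people who record adverse events.

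At stake is the comparison of minor harms, which the protocol needs because it weighs POEM's expected efficacy against its harms. Serious events are less exposed: they are harder to miss and have their own reporting rule in section 7.3.3. Analysis cannot repair the problem afterwards, because events that were never elicited are not in the data. It has to be settled in the collection rule.

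**Working it through.** The protocol gives no detection rate for adverse events, so there is no figure of that kind to reproduce. The only plan figure used is the arm size: 56 / (1 - 0.10) = 62.2, rounded up to 63, as in section 4.4.

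**Step 1. Named contacts after treatment starts.**

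| | EBD | POEM |
|---|---|---|
| Treatment | session 1, session 2 | one procedure with stay up to 48 h |
| Further arm-specific contact | evaluation 7 days after session 2; possible third session or second series | none named before month 3 |
| Common to both | monthly Eckardt, home weight | monthly Eckardt, home weight |

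EBD has at least three arm-specific contacts, or four with a third session. POEM has one. The three-month visit may be two weeks early (Table 2), so its earliest date is about week 13 - 2 = 11, or day 77. Applying the two-week tolerance for monthly weight, the month-1 record falls on days 30 ± 14 = 16 to 44.

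**Step 2. Length of the recording window.** Days are counted from the first treatment session; any study procedure before it adds the same lead-in to both arms. Length = day of last protocol session + 30.

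- POEM: 0 + 30 = 30 days.
- EBD, two sessions: 14 + 30 = 44 nominally; 40 to 48 with 10-18 days; 37 to 72 with Table 2.
- EBD, three sessions (14 to 28 days more): 58 to 72 nominally; 54 to 76 with 10-18 days; 51 to 100 with Table 2.
- A relapse series extends or reopens the window; the text does not say which.

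Section 7.2.1 counts events whether or not they are related to treatment. Unrelated events at one constant daily rate, fully reported, would therefore be recorded 44 / 30 = 1.47 times as often in a two-session EBD child.

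**Step 3. Illustration of detection, on assumed values only.** Let r = 0.30 be the true risk of a minor event in both arms, f the share arising within 48 hours, and s the chance that a family volunteers an event. Let d = 0.95 be detection during the POEM stay, and c = 0.9 × 0.6 = 0.54 the chance that an unreported EBD event surfaces at a later contact.

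- POEM recorded = r[f·d + (1 - f)·s]
- EBD recorded = r[1 - (1 - s)(1 - c)]

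Worked case, f = 0.3 and s = 0.4: POEM 0.30 × (0.285 + 0.280) = 16.9%; EBD 0.30 × (1 - 0.6 × 0.46) = 21.7%; difference -4.8 points.

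| f | s = 0.4 | s = 0.6 | s = 0.8 |
|---|---|---|---|
| 0.3 | -4.8 | -3.3 | -1.9 |
| 0.5 | -1.5 | -1.2 | -1.0 |
| 0.8 | +3.5 | +1.9 | +0.4 |

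(POEM minus EBD, percentage points.) With 63 per arm the extremes are 0.048 × 63 = 3.0 children fewer and 0.035 × 63 = 2.2 children more in the POEM arm.

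The sign changes where f = 0.54(1 - s) / (0.95 - s): 0.324 / 0.55 = 0.59 at s = 0.4, 0.216 / 0.35 = 0.62 at s = 0.6, and 0.108 / 0.15 = 0.72 at s = 0.8. The protocol gives no value for f. The model also gives EBD no credit for observation around its own sessions, which are done under general anaesthesia; adding it would make the differences more negative.

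**The case against.** A reader might infer that POEM's minor harms are simply under-counted and that the safety comparison is tilted towards the investigational arm. Assume a true 20% rate of post-discharge events in both arms, 90% found where staff see the child and 50% where they do not. The arms then show 0.20 × 0.90 = 18% and 0.20 × 0.50 = 10%, a gap of 8 points, or 4 points if 70% are volunteered (0.20 × 0.70 = 14%). The protocol does not support this as a statement about harm overall:

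- The detection rates have no source, and looking only at post-discharge events leaves out the period when POEM children are watched most closely.
- Section 7.2.1 also counts what staff observe. The mild POEM complications cited in section 9.4 are intraoperative and would be seen directly. Section 1 notes that EBD can be an outpatient procedure, although that is general background.
- Part of any EBD excess is real exposure to repeated procedures, not detection.

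A second tempting reading is that whatever a POEM family reports after day 30 is lost. Section 7.3.1 limits when an event occurs, not when it is reported. A day-10 event mentioned at month 3 is still recordable; the weakness is recall.

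Two further objections have force. Complications are a separate secondary outcome, listed with the 3, 6 and 12 month time points and not restricted to spontaneous reports (sections 2 and 6.1.2). That is a partial safeguard, but no method of asking is given, and a first inquiry at about week 11 is a weak way to find a brief fever. The visit chart in Figure 2 is also largely not shown, and the mode of the EBD day-7 evaluation is not stated, so an extra contact in the chart cannot be excluded.

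What stands against all of this is narrower: capture is passive, and opportunity and window length differ by arm.

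**Conclusion.** The point holds as a weakness of the collection rule, not as a contradiction in the protocol. Minor events arising after discharge are likely to be detected less completely after POEM, because EBD children are scheduled to be in contact again while such events are recent. For minor harm overall, the direction of bias is uncertain: closer in-hospital observation after POEM pulls the other way, and the balance depends on event timing that the protocol does not give.

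The firm figures are the window lengths: 30 days for POEM against 44 nominally for two-session EBD, and up to 100 for three sessions within Table 2. The range of -4.8 to +3.5 points is an illustration on assumed rates, not an estimate. It amounts to two or three children per arm, but minor harms in 63 children per arm will be few, so a shift of that size can change how the comparison reads. The conclusion assumes that the missing part of Figure 2 adds no harms inquiry or extra POEM contact. Serious events are less affected.

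**What to change.** 1. **Section 7.2.1.** Add one short list of post-procedure events, identical in both arms and asked at the same times counted from the first procedure. Attach it to the monthly Eckardt and weight record that both arms already complete. The month-1 record is the key one. Each record should ask about the whole period since the first procedure or the previous record, so that a month-1 record taken as early as day 16 leaves no gap.
2. **Section 7.3.1.** Record and summarise adverse events over one common window from the first procedure, with its length fixed in advance. Thirty days would leave out a second EBD session held as late as day 42, which Table 2 accepts. Seventy-two days covers every two-session course within Table 2, and 100 days every three-session course. State how events after a relapse series are handled.
3. **Section 6.1.2.** Keep staff-observed and volunteered complications in the between-arm comparison, each marked by how it was detected (asked, volunteered, observed).

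Two alternatives should be avoided. Asking after each treatment session would question EBD families at least twice and POEM families once. Setting unsolicited events aside could remove the intraoperative POEM complications from the comparison.

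The cost is a few extra questions on an existing record, and recording that runs beyond day 30 in the POEM arm. More minor events will be recorded in both arms. No treatment or visit changes.
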